### Primary outcome measure

#### CPM

The CPT will be used to measure CPM. For the conditioning stimulus, the participants’ non-dominant hand will be immersed in a bucket with temperature-controlled cold water (1 °C–4 °C), monitored by a thermometer for up to 1 min. The participant has to remain with the hand immersed in water without making muscle contractions or changes in position. Withdrawal from the water will be allowed if the patient can no longer tolerate the painful stimulus. This test will be conducted in a room with controlled room temperature, humidity, lighting, and noise.

Using a digital pressure algometer, the pressure pain threshold (PPT) will be performed in the forearm regions and tibialis anterior muscle of the dominant limbs before and after 1 min of the CPT. The tibialis anterior muscle and the distal part of the dorsal forearm, which had not been immersed in water, will be evaluated because of the lack of their relationship with the participants’ musculoskeletal complaints.

The operation of the pressure algometer and PPT measurement will be explained to the patients, and a practice test will be conducted on the patients’ dominant forearm to ensure that the test has been understood. Force will gradually be increased [1 kg-force/s] until the feeling of pressure changes to pain. The PPT will be recorded in kilograms force [Kgf]. The PPT will be repeated three times and the mean will be calculated to give the baseline PPT. The efficiency of the descending nociceptive inhibitory system will be evaluated by calculating the difference between PPT values in CPT (final cost − initial value) [41].

### Secondary outcomes

Executive functions will be evaluated using the letter–number sequencing subtest and the Stroop neurophysiological test.

#### Letter–number sequencing subtest

The letter–number sequencing subtest in WAIS-III will be used to evaluate working memory. In this task, the participants need to listen to a series of alphanumeric characters and repeat the characters back verbally in a specific order (numbers first in the ascending order, followed by letters in the alphabetical order). The test items will be presented in the same order for all participants. The researcher will read the test items aloud, at approximately 1 s per character. The participants will be asked to record their responses by speaking aloud to the researcher, and the researcher will mark the test stimuli as completely correct or incorrect. This subtest involves 21 items. The outcome is expressed as a scaled score; each correct response shall receive 1 point, and the maximum possible score is 21 [42].

#### Stroop neurophysiological test

The test stimuli will be presented on a computer screen. A total of 40 items will be presented in 8 rows of 5 items each. The items and the print colors will appear in a random order. The first subtask will show color words in a random order (red, blue, yellow, and green) printed in black ink. The second subtask will display solid color patches in one of these four basic colors. In the third subtask, the color words will be printed in an incongruous ink color. For example, the word *yellow* will be printed in red ink. The participants will be allowed to identify the colors in English/Hindi. No time limit will be assigned to complete a subtask. The time required in seconds to complete each Stroop subtask will be recorded using a stop clock (Stroop I, Stroop II, and Stroop III) [43]. The interference score is determined by subtracting the mean score of the first and second subtest from the amount of time required to complete the third subtest.

#### NPRS

The NPRS is a basic instrument that may be administered even to low-literate adults through a verbal face-to-face interview or telephonic interview; the adults can also self-report their responses [44]. The amount of pain felt by a patient will be subjectively estimated by marking their pain level on an 11-point, 0-to-10 NPRS, with 0 and 10 corresponding to no pain intensity and maximum pain intensity, respectively [45].

#### Oswestry Disability Index

The ODI is a 10-item questionnaire used for assessing function in the activities of daily living for LBP patients. Each item in the ODI receives a score between 0 and 5. The final score will be transformed into a percentage score. We will use the modified version of the ODI where the section on employment/homemaking ability will replace the section on sex life. This modified version has a high reliability (ICC = 0.90) and responsiveness [46]. The Hindi version of the ODI is a valid and reliable instrument for measuring disability in LBP patients [47].

### Quality of life

The participants’ QoL will be assessed using the abbreviated WHOQOL-BREF questionnaire. This questionnaire comprises 24 items divided across the 4 domains of physical health, psychological health, social relationships, and environmental health. Each item is rated on a 1–5 Likert scale. The mean score of items within each domain is summed up, and the scores are transformed on a scale from 0 to 100 [48]. The Hindi version of the WHOQOL questionnaire is effective for evaluating QoL in India’s healthcare settings [49].

### Isometric muscle strength (spine extensors, gluteus maximus, gluteus medius, and hip lateral rotators)

Isometric muscle strength of trunk extensors, transverse abdominis, obliques, gluteus medius, gluteus maximus, and lateral hip rotators will be assessed using a pressure biofeedback unit (PBU) (Chattanooga INC). Once the PBU is inflated to 70 mm Hg, the participants will be instructed to contract the specific muscles. Readings will be taken at the completion of a 10-s contraction. Two submaximal force tests will be conducted to help the participants become familiarize with each test position, followed by two repetitions with maximum isometric contraction for each muscle group. The average of the two maximum contractions will be used for analysis [50].*Transversus abdominis* will be tested in the prone position. The inflated cuff will be positioned beneath the abdomen at the level of the anterior superior iliac spine. The patient will be instructed to draw-in the lower abdomen without moving the upper stomach, back, or pelvis [50].Abdominal obliques [bilateral OE and OI] and back extensors [ES and multifidus] will be tested in the supine lying position. The inflated cell will be placed at the level of the posterior superior iliac spine.*Abdominal obliques*. The participants will be instructed to gently press the cell, as if to straighten the spine. For back extensors, the participants will be instructed to lift the weight off the cell [51].The *gluteus medius muscle* will be evaluated in the side-lying position with the test leg upward. The hip will be placed in neutral adduction and extension [52], and the inflated cuff will be placed 5 cm above the lateral condyle of the femur. The participants will be asked to lift the leg against the resistance of the examiner’s hand.The *gluteus maximus muscle* will be evaluated in the prone position with the hip in neutral and knee flexed to 90 degrees [53]. The inflated cuff will be placed 5 cm above the popliteal region and will attempt to lift the leg against the resistance of examiner’s hand.The *hip lateral rotator muscles* will be assessed in the high sitting position [54]. The inflated cuff will be placed 5 cm above the medial malleolus. The patients will be instructed to externally rotate the hip against a resistance in an opposite direction.

### Participant timeline {13}

The participant timeline is presented in Table 3.

**Table 3 Tab3:** Summary of data collection

	**Enrolment**	**Baseline/assessment**	**Follow-up**	**Exit**
Subject demographics	X	X	X	X
Outcome measures	X	X	X	X
Medical history	X			
Assessment details	X	X	X	
Patient status	X	X	X	X
Events	X	X	X	X
Protocol deviations	X	X	X	X

### Sample size {14}

The sample size was calculated based on the inhibitory effect of the CPT on the PPT, assuming a standard deviation of 100 kPa for the inhibitory effect across all three exercise groups. A sample size of 30 participants per group provides 87% power for an independent *t*-test at a 2-sided alpha of 0.05 to detect a difference in inhibition of 80 kPa [17] when assuming a minimum difference of 0.47 (equivalent to 10% change) as clinically relevant for the CPM effect [55]. Therefore, anticipating a 30% dropout rate, 43 participants will be recruited for each group.

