**Methods:**

The trial is a randomized, controlled, multi-center study with four experimental groups and one healthy control group. Both the researchers and the people in the study will be blinded to the results. This paper describes the protocol for a trial examining the effects of 12-week individualized, twice-weekly exercise sessions lasting 30 to 60 min in persons with CLBP, who are positive for CS. Participants will be randomized to receive either patient education with motor control exercises (MCE), superficial strengthening (SS), aerobic exercises (AE), or patient education alone. Another group comprised of healthy volunteers will serve as controls. The primary outcomes are changes in CPM outcomes as measured by the cold pressor test (CPT). The secondary objectives are to evaluate executive functioning, pain, disability, quality of life, and spine muscle strength. The outcomes will be measured at 3 months and at a 6-month follow-up.

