## Introduction

### Background and rationale {6a}

Chronic low back pain (CLBP) refers to low back pain (LBP) that is persistent and incapacitating for more than 3 months [1] and is unrelated to underlying illnesses such as an infection, tumor, or fracture [2]. Because the causes of most CLBP conditions are unknown, they are categorized as non-specific CLBP (NSCLBP) [3]. Studies have indicated abnormal cortical function in CLBP patients including reduced left dorsolateral prefrontal cortex activity [4]; disruption of executive functions such as multitasking ability [5], sustained attention and working memory [6, 7]; longer processing time [8]; and substantial disturbances in mental flexibility, delayed memory, and psychomotor speed [9].

The role of pain sensitivity in the development and maintenance of chronic pain states and its influence on patient recovery are unclear and thus being investigated. Impaired functioning of descending anti-nociceptive mechanisms and activation of the descending and ascending pain facilitatory pathways facilitate overall pain transmission. Central sensitization (CS) is the increased responsiveness of nociceptive neurons in the central nervous system (CNS) to their normal or subthreshold afferent input [10]. Conditioned pain modulation (CPM) is extensively used to measure CS-associated musculoskeletal pain and refers to the quantitative sensory test used to assess the functionality of endogenous pain inhibition in the CNS [11]. CPM is directly related to the cognitive performance and self-reported health-related quality of life (QoL) [12].

Although persons with chronic pain are believed to have lower CPM inhibition, Sluka (2016) reported that some individuals with fibromyalgia and healthy persons exhibit normal and abnormal responses to CPM, respectively [13]. Evidence for CPM alterations in CLBP patients is mixed, with studies revealing impaired [14], normal [15], and facilitated [16] CPM compared with healthy controls. Mlekusch et al. (2016) evaluated endogenous pain modulation by using the cold pressor test (CPT) in persons with and without LBP and reported that the CPM effect declined more rapidly in the LBP group than in the normal population [17].

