### Trial design {8}

This is a randomized, controlled, double-blinded study determining how CPM changes in response to three types of active exercises in CS-positive CLBP patients. Participants will be randomized to undergo 12 weeks of the motor control exercise (MCE), superficial strengthening (SS), or AE combined with patient education or patient education alone. This active treatment concurrent control design will be used to demonstrate superiority of one exercise group over another. All patients will be allocated in a 1:1:1:1 ratio using random number tables. All participants will receive advice to stay active. Another no-pain control group will also be recruited. The intervention will be provided for 12 weeks. An independent assessor will collect data at baseline (t0), after intervention at 3 months (t1), and at the 6-month follow-up (t2). Outcome measures include CPT for measuring CPM, letter–number sequencing subtest in the Wechsler Adult Intelligence Scale-III Edition (WAIS-III), Stroop neurophysiological test, QoL assessed using the abbreviated WHOQOL-BREF questionnaire, isometric muscle strength of spine and hip muscles, the Oswestry Disability Index (ODI) questionnaire, and the Numerical Pain Rating Scale (NPRS). Table 1 and Fig. 1 present the study design and flowchart, respectively. The research ethics approval was granted by the Integral University, India (IIAHSR/DO/PT/2022/23), and Composite Regional Centre for Skill Development, Rehabilitation, and Empowerment of Persons with Disabilities, India (CRCL/Ph.D. Data Collection/2021–22/1556). The study is designed according to the Consolidated Standards of Reporting Trials (CONSORT) guidelines and reported according to the Standard Protocol Items: Recommendations for Interventional Trials (SPIRIT) checklist. The study will use a 5 (between subjects − type of exercise interventions: MCE vs. AE vs. SS vs. patient education vs. no-pain control) × 3 (within subjects − time: before vs. after vs. 3 months after the intervention) mixed design.

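### The 87% power is calculated for a CPM value, while the declared primary outcome is a change in CPM analysed by repeated measures; the plan does not show that the figure carries over

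*Protocol article*

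**What the plan says.** Sample size {14} bases the calculation on how far the cold pressor test raises the pressure pain threshold, "assuming a standard deviation of 100 kPa for the inhibitory effect across all three exercise groups". The power statement concerns a two-group *t*-test and opens "A sample size of 30 participants per group provides 87% power for an independent". The effect that this test is meant to find is given in these words: "at a 2-sided alpha of 0.05 to detect a difference in inhibition of 80 kPa". The 80 kPa carries a literature citation. Background and rationale {6a} describes that cited study as one that "evaluated endogenous pain modulation by using the cold pressor test (CPT) in persons with and without LBP", and mentions no change over a course of treatment.

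The section on the primary outcome measure (CPM) defines the inhibitory effect as the threshold after the cold immersion minus the threshold before it. It is therefore measured within one session.

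The outcome itself is described as a change. The Abstract (Methods) says "The primary outcomes are changes in CPM outcomes as measured by the cold pressor test (CPT"), and Trial design {8} presents the study as "determining how CPM changes in response to three types of active exercises". Statistical methods {20a,b} applies repeated-measures ANOVA to CPM in a five-group by three-visit mixed design, followed by Tukey comparisons. It mentions no baseline adjustment, no between-visit correlation and no SD of change. It does not say which contrast within the ANOVA is primary.

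**The concern.** The quantity powered and the quantity declared primary do not match. A CPM value from one visit and the difference between two such values generally have different SDs. How they relate depends on how strongly CPM at one visit predicts CPM at the next. In a group-by-visit design the interaction compares change between groups, which is how the Abstract and Trial design {8} describe the aim. The *t*-test in Sample size {14} compares a CPM value between two groups at SD 100 kPa.

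A reader will take 87% as the power for the primary outcome. If the analysis is in effect a comparison of changes and the between-visit correlation is low, the power is materially below that, before any allowance for multiple comparisons. If the correlation is high, the power is better than stated. The article gives no basis for choosing between these cases.

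This point is separate from the choice between a *t*-test and Tukey comparisons, and from the 0.47 threshold quoted in the same paragraph.

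**Working it through.** **Inputs from the article.** Evaluable n = 30 per group, difference 80 kPa, SD 100 kPa, two-sided alpha 0.05, independent *t*-test, 30% dropout (all Sample size {14}); equal allocation (Trial design {8}).

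**Input not in the article.** The correlation r of CPM between visits. It is assumed below over a range from 0 to 0.7.

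**Step 1: the plan's own figure.** Standard error = 100 × √(2/30) = 25.8 kPa, and 80 / 25.8 = 3.10. By normal approximation, power = Φ(3.10 − 1.96) = 87.3%. The exact noncentral *t* with 58 degrees of freedom gives 86.1%. Dropout: 30 / (1 − 0.30) = 42.9, rounded up to 43. Both stated figures reproduce, so there is no arithmetic error in them.

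**Step 2: three contrasts, same inputs.** Randomised groups have the same expected baseline. A between-group difference of 80 kPa at week 12 is therefore also an expected 80 kPa difference in change, and only the SD differs. Assume 100 kPa is the SD at each visit and, for the third contrast, equal correlations between all visits.

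- Change from baseline to week 12: SD = 100 × √(2(1 − r)). It equals 100 kPa at r = 0.5.
- Week-12 CPM adjusted for baseline: SD = 100 × √(1 − r²). It never exceeds 100 kPa.
- Mean of both post-baseline visits minus baseline: SD = 100 × √(1 + (1 + r)/2 − 2r) = 100 × √(1.5(1 − r)). It equals 100 kPa at r = 1/3.

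Exact *t* power, n = 30 per group, 80 kPa, unadjusted for multiplicity:

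| r (assumed) | SD of change (kPa) | Power, change to week 12 | SD, baseline-adjusted (kPa) | Power, baseline-adjusted | Power, mean of two post visits minus baseline |
|---|---|---|---|---|---|
| 0 | 141.4 | 57.7% | 100.0 | 86.1% | 70.1% |
| 0.2 | 126.5 | 67.3% | 98.0 | 87.5% | 79.4% |
| 0.3 | 118.3 | 73.1% | 95.4 | 89.1% | 84.5% |
| 0.4 | 109.5 | 79.4% | 91.7 | 91.4% | 89.5% |
| 0.5 | 100.0 | 86.1% | 86.6 | 94.0% | 94.0% |
| 0.7 | 77.5 | 97.6% | 71.4 | 98.9% | 99.5% |

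Comparing week-12 CPM alone, without adjustment, gives 86.1% whatever r is.

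**Step 3: reading the table.** The stated figure is right for week-12 CPM alone and conservative for the baseline-adjusted comparison. For the two change contrasts it is optimistic below the break-even correlation and pessimistic above it. The break-even itself depends on the contrast (0.5 or 1/3).

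**The case against.** The strongest reply is that no loss of power has been demonstrated. The article names no change-score test as primary. Statistical methods {20a,b} applies the ANOVA to CPM itself, uses Tukey comparisons for differences between groups, and defines effect size as a between-group mean difference in outcomes over a combined SD. All of this can be read as comparing CPM values between groups, which is what was powered. The formal endpoint in Outcomes {12} is a 10% change in threshold within the cold pressor test, and its phrase about baseline to week 12 attaches grammatically to the pain rating, not to CPM. Sample size {14} does not say whether 100 kPa describes a value or a change. A condensed article may also leave the correlation to a fuller document.

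Much of this stands. The single-visit reading of 100 kPa is natural but inferred. A reader might conclude that 87% holds only if r is at least 0.5, or that the trial is underpowered. The documents support neither: 0.5 is the break-even for one contrast only, no value of r is given, and above the break-even the stated power is too low rather than too high.

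The reply does not remove the mismatch. The article itself states a power, an SD and a test for one quantity and then declares a change as the outcome, with a group-by-visit analysis. Neither analysis that would secure about 86% at any r (week-12 CPM alone, or adjusted for baseline) is named as the primary contrast. The objection is therefore to what the article asserts, and goes beyond a missing detail.

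**Conclusion.** The concern holds as a mismatch. The 87% is correctly calculated for a two-group *t*-test on a CPM value with SD 100 kPa, but it is not shown to apply to the declared outcome, a change in CPM analysed by repeated measures over three visits. If the contrast is change from baseline to week 12, power with 30 per group runs from 58% at r = 0 to 98% at r = 0.7 and matches the stated figure at r = 0.5. This rests on three assumptions: 100 kPa is a single-visit SD, it is the same at both visits, and r lies in the assumed range. Other contrasts have other break-even points. The direction of any error is unknown, so this is not a finding that the trial is too small. It deserves action because an analysis using data already collected makes the stated power safe at any r.

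**What to change.** Make the primary contrast the difference between randomised groups in week-12 CPM adjusted for baseline CPM, by ANCOVA or an equivalent baseline-adjusted model. State in Sample size {14} that 100 kPa is taken as a conservative SD for this contrast and that power is at least about 86% at any r, before multiplicity adjustment. This assumes, as above, that 100 kPa describes CPM at a single visit; the sponsor should confirm that.

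If a change-score or group-by-visit contrast is kept, name it, say what the 100 kPa describes, and give either an SD of change or the power over a stated range of r, for example 0.2 to 0.7.

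The cost is a revised sample-size paragraph and a sentence in the statistical methods. Baseline CPM is already scheduled, so no further measurements or participants are needed and the sample size stays as it is. If a change contrast is kept, the reported power may look less favourable.

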### Statistical methods

#### Statistical methods for primary and secondary outcomes {20a,b}

The Shapiro–Wilk test will be used to assess the normality of the distribution of the data. A one-way analysis of variance (ANOVA) will be used to compare baseline characteristics between the groups. Descriptive statistics will be used to calculate the mean values of all outcome variables collected. A repeated measure ANOVA statistic will be used to evaluate the effect of three types of exercise interventions on CPM, neurophysiological outcomes, pain, disability, strength measures, and QoL. The study will use a 5 (between subjects – type of exercise interventions: AE vs. MCE vs. SS vs. patient education vs. no-pain control) × 3 (within subjects – time: before vs. after vs. 3 months after the intervention) mixed design. Tukey’s post hoc analysis will be conducted to establish differences between the groups. Effect size will be estimated by dividing the mean difference in outcomes between the intervention and control groups by the combined standard deviation of the two groups [56].

The primary outcome will undergo a per-protocol analysis. Pearson correlation analysis will be performed to determine the relationship between patient characteristics (Table 4), CPM, executive functioning, pain, strength measures, disability, and QoL. Multiple linear regression analysis will be used to deduce the characteristics of individuals responding positively to exercise interventions. For all measurements, *p* will be considered significant, if it is < 0.05. The data collected will be analyzed using SPSS (Statistical Program for the Social Sciences) 16.0 (IBM Corp., Armonk, NY).

**Table 4 Tab4:** Summary of patient characteristics to be collected

Characteristics	CLBP group	Control group
Age (years)	X	X
Gender (male/female)	X	X
Pain episode duration (weeks)	X	X
Body mass index (kg/m^2^)	X	X
Education level (yes/no; school incomplete, completed secondary school, completed diploma/completed bachelors and above)	X	X
Employment status (yes/no; employed (full or part-time), unemployed, retired)	X	X
Marital status (yes/no; married/separated/ divorced, single)	X	X
Personal behaviors Alcohol status (yes/no) Smoking status (yes/no)	X	X
Comorbidities	X	X
Fear avoidance behavior	X	X
Perception of improvement	X	X

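### The stated 87% power is correct for one unadjusted t-test at 80 kPa, but it is not the power of the planned Tukey comparisons, nor of the 0.47 threshold named in the same sentence

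*Protocol article*

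**What the plan says.** Sample size {14} plans on the inhibitory effect of the cold pressor test on the pressure pain threshold (PPT), "assuming a standard deviation of 100 kPa for the inhibitory effect across all three exercise groups". It then states: "A sample size of 30 participants per group provides 87% power for an independent" t-test. That test is two-sided at the 5% level, and the target is 80 kPa. The sentence ends by tying this to a relevance threshold, "when assuming a minimum difference of 0.47 (equivalent to 10% change) as clinically relevant for the CPM effect". A 30% dropout allowance takes 30 per group to 43.

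The planned analysis is different. Trial design {8} aims to show that one exercise group is superior to another and names no single pair. Statistical methods {20a,b} specifies a mixed ANOVA with five groups (four randomised arms and a no-pain control) and three time points, after which a Tukey "post hoc analysis will be conducted to establish differences between the groups".

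On units, the CPM section says "The PPT will be recorded in kilograms force [Kgf"], whereas the planning difference and SD are in kPa. Outcomes {12} and Statistical methods {20a,b} both use a 10% change in PPT as a success criterion.

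**The concern.** A power statement tells the reader how likely the planned comparison is to detect the planned difference. Here the number belongs to a different test from the one that will compare the groups. Tukey's procedure needs a larger test statistic for each pair because it controls error over all pairs: 3 among the exercise arms, 6 among the randomised arms, 10 among all five groups. The sample size section does not allow for this.

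The sentence also places a second difference, 0.47, beside the 80 kPa. A reader will naturally take 87% as the power at the clinically relevant threshold, although the calculation uses 80 kPa alone. Because 0.47 has no unit, the document does not let anyone set the two side by side.

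The primary objective is whether exercise types differ in their effect on CPM. If 87% is taken at face value, a non-significant Tukey comparison would be given more weight as evidence of no difference than the design supports.

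**Working it through.** **Inputs.** From Sample size {14}: n = 30 evaluable per group, difference 80 kPa, SD 100 kPa, two-sided alpha 0.05, 30% dropout, threshold 0.47. From Statistical methods {20a,b}: Tukey comparisons and five groups. From Trial design {8}: four randomised arms. Assumed, because the document does not say: a single time point, and, for one reading of 0.47, a 1 cm² probe.

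**1. The plan's own figure.** The standardised difference is d = 80/100 = 0.80. The noncentrality is d × √(n/2) = 0.80 × √15 = 3.098.
- Normal approximation: Φ(3.098 − 1.960) = 87.3%.
- Exact noncentral t, 58 df, critical value 2.002: 86.1%.
- Dropout: 30/0.70 = 42.9, rounded up to 43.

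The 87% and the 43 both reproduce.

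**2. Same inputs, Tukey critical value.** The critical value is the 0.95 quantile of the studentised range for k groups divided by √2, with pooled error df = 30k − k. The noncentrality stays at 3.098.

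| Groups in the Tukey family | df | Critical value | Power for a given pair at 80 kPa |
|---|---|---|---|
| 3 (exercise arms) | 87 | 2.38 | 76.1% |
| 4 (randomised arms) | 116 | 2.61 | 68.8% |
| 5 (as in the ANOVA) | 145 | 2.76 | 63.2% |

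The difference detectable for a given pair with 80% power is about 89 kPa (four groups) or 93 kPa (five groups).

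**3. Power at 0.47, if it is a between-arm difference.** Two readings:
- SD units: d = 0.47.
- kgf on an assumed 1 cm² probe: 0.47 × 98.07 = 46.1 kPa, so d = 0.461.

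| Test | d = 0.461 | d = 0.47 |
|---|---|---|
| Unadjusted t-test | 41.9% | 43.3% |
| Tukey, 4 groups | 21.1% | 22.1% |
| Tukey, 5 groups | 16.9% | 17.7% |

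The two readings give nearly the same answer, so the result does not depend on choosing between them. It does depend on 0.47 being a difference between arms.

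**4. A different definition of power.** Under the same single-time-point simplification, the chance that Tukey declares at least one pair different depends on the pattern of means. If one arm differs from all the others by 80 kPa, it is about 89% for three, four or five groups. If only two arms differ by 80 kPa and the rest lie midway, it is about 73% for four groups and 69% for five.

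**The case against.** The strongest reply is that nothing has been miscalculated. The section openly names its basis (a t-test, two-sided 0.05, 80 kPa) and makes no claim about Tukey. That stands: this is a mismatch between the power statement and the planned analysis, not an arithmetic error.

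Second, a reader might infer that the trial's power simply is 63–69%. The documents do not support that. Those figures are for one given pair at one time point. The objective can be read as asking whether any exercise types differ, and the chance of declaring at least one pair reaches about 89% under some patterns of means. The planned model uses repeated measures, and its effective SD depends on a within-person correlation that the protocol does not give. This limits the Tukey figures but does not rescue the 87%, because the protocol claims no gain from repeated measures and its superiority aim concerns one group against another.

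Third, a reader might conclude that the trial will more likely than not miss a difference at its own relevance threshold. That goes too far. The 10% criterion can be read as a change within a person, since the CPM section defines the measure as final minus initial PPT, and the source for 0.47 is not available here. Planning for an expected effect larger than the smallest relevant one is also a legitimate choice. The 42–43% and 17–22% figures are therefore conditional. What stands without condition is that 0.47 has no unit and no stated meaning, and that 87% was not calculated for it.

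Fourth, the 89–93 kPa must not be read as the range a null result leaves open. It is a detectable difference. What a result excludes depends on the observed difference and its interval; on the planning inputs the Tukey 95% half-width for four arms is about 2.61 × 100 × √(2/30) = 67 kPa.

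**Conclusion.** The point holds in a limited form. The 87% is right for one unadjusted two-sided t-test at 80 kPa, SD 100 kPa and 30 evaluable per group. It is not the per-pair power of the planned Tukey comparisons, which on the same inputs is about 76%, 69% or 63% for three, four or five groups. These figures assume a single time point and 30 completers per group.

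The 87% also does not apply to 0.47, which the same sentence attaches to it. If 0.47 is a between-arm difference, in SD units or in kgf on a 1 cm² probe, power is about 42–43% unadjusted and 17–22% with Tukey over five or four groups. If it is a within-person criterion, those figures do not apply, and the link to 87% has no stated basis.

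The fault lies in what the statement can be taken to mean. The documents do not support saying that the sample size was computed wrongly, or that the trial's overall power is any one of the lower figures.

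**What to change.** Amend Sample size {14}, leaving the number recruited unchanged:

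- State that 87% is for a single unadjusted two-group comparison at 80 kPa with SD 100 kPa.
- Add the per-pair power under Tukey: about 69% for the four randomised arms and 63% for the five groups in the ANOVA, calculated at one time point without any repeated-measures gain.
- Give the unit of 0.47 and say whether it is a within-person change or a difference between arms.
- Put the SD, the 80 kPa, the 0.47 and the recorded PPT on one scale. Converting between kgf and kPa requires stating the probe area.
- If 0.47 is a between-arm difference, report the power at that value separately.
- If the detectable difference is given (about 89–93 kPa with 80% power under Tukey), describe it as that only, and say that a null result will be interpreted from the observed confidence intervals.

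This is a change of text. It does not alter recruitment, conduct or the analysis. Its cost is that the stated power becomes less favourable.
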